### Ordinal outcomes

Ordinal outcomes will be presented as proportions for each level and for simplicity also dichotomized into favourable and unfavourable. For mRS, 0–2 is favourable, and 3–6 is unfavourable [13, 14]; for GOSE, > 5 is favourable, and ≤ 5 is unfavourable [15]. Ordinal outcomes will be analysed using ordinal logistic regression with stratification variables as fixed effect and site as random effects [27, 28]. The results will be presented as relative risks (RRs) and confidence intervals for improving one level on the ordinal outcome [29].

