**Exploratory outcomes**	
Functional outcome according to modified Rankin Scale (mRS) at 6 months (1–6 scale)	Ordinal
The remaining dimensions of EQ-5D-5L (mobility, self-care, usual activities, pain/discomfort, and anxiety/depression) at 6 months (1–5 levels)	Count
Glasgow Outcome Scale Extended (GOSE) at 6 months (1–8 scale)	Ordinal
Reason for failure of EVD cessation (ICP elevation, drop in GCS by 2 points or more, and/or clinical deterioration)	Count
GCS on discharge from the Neuro Intensive Care Unit and Neurosurgical department	Count
Length of stay in Neuro Intensive Care Unit	Count
Length of stay in hospital	Count

*aSAH* aneurysmal subarachnoid haemorrhage, *EVD* external ventricular drain, *GCS* Glasgow Coma Scale, *ICP* intracranial pressure, *SAE* serious adverse events, *VP-shunt* ventriculoperitoneal-shunt

Secondary outcomes are:

Number of serious adverse events (SAE) not including mortality and defined according to International Conference of Harmonization of Good Clinical Practice (ICH-GCP) within 6 months (count outcome)Health-related quality of life (EQ-5D-5L) at 6 months [11] with the primary assessment being self- assessment of own health (EQ VAS; 0 to 100 point scale) (continuous outcome)Fatigue Severity Scale (FSS) mean score at 6 months [12]

Exploratory outcomes are:

Functional outcome according to modified Rankin scale (mRS) at 6 months [13, 14] (1–6 scale) (ordinal outcome)The remaining dimensions of EQ-5D-5L (mobility, self-care, usual activities, pain/discomfort, and anxiety/depression) at 6 months [11] (1–5 levels) (count outcome)Glasgow Outcome Scale Extended (GOSE) at 6 months [15] (1–8 scale) (ordinal outcome)Reason for failure of EVD cessation (ICP elevation, drop in GCS by 2 points or more, and/or clinical deterioration)GCS on discharge from the Neuro Intensive Care Unit and Neurosurgical departmentLength of stay in Neuro Intensive Care UnitLength of stay in hospitalEach component of the primary outcome will be analysed as exploratory outcomesEach component of the composite outcome will be analysed as exploratory outcomes

VP-shunt implantation is the consequence of failed EVD discontinuation and as such is included in the composite endpoint. The explanatory outcomes cover among other the reasons for the EVD discontinuation to be deemed a failure, e.g. intracranial hypertension or clinical deterioration.

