### Dichotomous outcomes

Dichotomous outcomes will be presented as proportions for each group with an annotation in the tables of the percentage of missing data per group. Dichotomous outcomes will be analysed using mixed-effects logistic regression with stratification variables as fixed effect and site as random effects. We will estimate the marginal effects to obtain RRs and confidence intervals of the RRs (based on ‘nlcom’ from Stata (StataCorp LLC, Texas, USA)) or G-computation in R. We have chosen to—as a primary analysis—investigate our count outcomes without dichotomisation. Inappropriate dichotomisation—even though widely used—results in lower power and possibly also faulty results [28, 30, 31].

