#### Assessments of underlying statistical assumptions

The chosen analyses have few assumptions, with the main assumptions being related to the linear and logistic regressions [23, 33]. The variables included in the *linear regression models* will be visually assessed for normal distribution using histograms and quantile–quantile plots of the residuals, and for homogeneity using residuals plotted against covariates and fitted values, with the possibility of a logarithmic transformation or applying robust standard errors to minimise deviations from the model.

The deviance divided by the degrees of freedom for *logistic regression model* will be calculated to assess relevant overdispersion. The method used will be mixed effects logistic regression with stratification variables as fixed effect and site as random effects, and if few or zero events are identified, the analyses will instead be carried out using Fisher’s exact test. The robustness of the confidence intervals and *p*-values might be affected by the small sample size, and these will be interpreted with caution. Furthermore, the ordinal logistic regression assumes proportionality of odds across response categories (i.e. the magnitude of improvement or hazard, with a treatment, would be similar irrespective of baseline severity, age, etc.) [27, 29].

If assumptions for ordinal logistic regression are not met, we will use partial proportional odds model if applicable. If this is not possible, we will analyse the data as described for count outcomes.

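### Ordinal logistic regression of mRS and GOSE is to be reported as a relative risk for improving one level, but the model gives a common odds ratio to which no single relative risk corresponds

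*SAP article*

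**What the plan says.** Under Ordinal outcomes the model is set: "Ordinal outcomes will be analysed using ordinal logistic regression with stratification variables as fixed effect and site as random effects". The same section then fixes how its result is reported: "The results will be presented as relative risks (RRs) and confidence intervals for improving one level on the ordinal outcome". It also gives proportions at each level and a favourable/unfavourable split, with mRS 0–2 against 3–6 and GOSE above 5 against 5 or below.

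The next section, Dichotomous outcomes, describes a route from a logistic model to a relative risk: "We will estimate the marginal effects to obtain RRs and confidence intervals of the RRs", using nlcom in Stata or G-computation in R. It is written for dichotomous outcomes only. Sensitivity analyses adds that the ordinal outcomes will also be analysed in dichotomised form.

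Assessments of underlying statistical assumptions says "the ordinal logistic regression assumes proportionality of odds across response categories" and explains this in brackets as meaning that "the magnitude of improvement or hazard, with a treatment, would be similar irrespective of baseline severity, age, etc". The remedy follows: "If assumptions for ordinal logistic regression are not met, we will use partial proportional odds model if applicable", and failing that, the method for count outcomes.

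Table 1 lists the outcome as "Functional outcome according to modified Rankin Scale (mRS) at 6 months (1–6 scale"; the list below the table repeats the 1–6 range.

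**The concern.** The model and the reporting rule do not match. A proportional-odds model yields an odds ratio for being in a better category, the same at every cut-point. A relative risk needs a named event, such as mRS 2 or lower, and improving one level is not such an event. Each scale is listed once, at 6 months, so the phrase cannot mean a change within a patient either.

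Two statisticians will analyse the data independently and, under Statistical reports, a significant difference between their results is settled by taking the more conservative one. With the quantity undefined, they could produce different numbers for the same outcome without either being in error.

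The explanation of the assumption matters because a change of model depends on it, and the article names no specific check of proportional odds. The mRS range matters because it sets the number of categories: six levels if 1–6, seven if 0–6.

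**Working it through.** **Inputs.** The model, the reporting rule and the scale ranges come from the article. It gives no odds ratio, no control distribution and no numerical result for mRS or GOSE, and Table 3 as shown has no row for either. There is therefore no figure of the plan's own to reproduce. The odds ratios (1.5 and 2.0) and control proportions below are assumptions, shown as a range. The algebra treats the control group as homogeneous and ignores the adjustment for strata and site.

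**Step 1. From odds ratio to relative risk at one cut-point.** Let p0 be the control proportion at or better than the cut. Under proportional odds the treated odds are OR × p0/(1 − p0), so

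RR = OR / (1 − p0 + OR × p0).

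**Step 2. One odds ratio, many relative risks.** Take seven levels with an even control distribution, so p0 = 1/7, 2/7, … 6/7. With OR = 1.5 the formula becomes 1.5/(1 + 0.5 × p0):

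| Cut | p0 | RR, OR 1.5 | RR, OR 2.0 |
|---|---|---|---|
| 1 | 0.143 | 1.40 | 1.75 |
| 2 | 0.286 | 1.31 | 1.56 |
| 3 | 0.429 | 1.24 | 1.40 |
| 4 | 0.571 | 1.17 | 1.27 |
| 5 | 0.714 | 1.11 | 1.17 |
| 6 | 0.857 | 1.05 | 1.08 |

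With control distributions skewed towards good or poor outcome, the relative risk runs overall from 1.03 to 1.46 for OR 1.5 and from 1.05 to 1.90 for OR 2.0. No single relative risk summarises the model.

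**Step 3. Size of the error if the odds ratio were labelled a relative risk.** Compare the relative excesses:

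(OR − 1)/(RR − 1) = (1 + p0 × (OR − 1))/(1 − p0).

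| p0 (assumed) | OR | RR | Ratio of excesses |
|---|---|---|---|
| 20% | 1.5 | 1.36 | 1.1/0.8 = 1.375 |
| 20% | 2.0 | 1.67 | 1.2/0.8 = 1.5 |
| 50% | 1.5 | 1.20 | 1.25/0.5 = 2.5 |
| 50% | 2.0 | 1.33 | 1.5/0.5 = 3.0 |
| 60% | 1.5 | 1.15 | 1.3/0.4 = 3.25 |
| 60% | 2.0 | 1.25 | 1.6/0.4 = 4.0 |

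At p0 = 5% the ratio is only 1.025/0.95 = 1.08 for OR 1.5. The multiplier depends almost wholly on the cut-point.

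**Step 4. The assumption.** Proportional odds concerns the outcome scale: the treatment odds ratio is the same at each cut. The bracketed text concerns patients: the effect is the same whatever their severity or age. Either can hold without the other. If the odds ratio were 1.5 at every cut below age 60 and 2.0 at every cut above it, odds would be proportional within each age group while the effect differed by age. If it were 1.5 at one cut and 2.0 at another in both age groups, the effect would not differ by age but proportional odds would fail.

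**Step 5. The mRS range.** Table 1 and the outcome list start at 1; the favourable category under Ordinal outcomes starts at 0. Both cannot be right, and the 0–2 / 3–6 split implies a 0–6 scale.

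**The case against.** The strongest reply is that the article never says the raw odds ratio will be printed as a relative risk. The section on dichotomous outcomes shows that its authors know a logistic coefficient must be converted, and the reporting rule cites a source not at hand. This stands in part. A reader might infer that effects on mRS and GOSE will be overstated 2.5 to 4 times. The documents do not support that: it requires plain relabelling, and it requires control proportions of 50% to 60%, which the article does not give. It does not rescue the reporting rule, because the described conversion covers dichotomous outcomes only and, if applied to an ordinal scale, would still need a cut-point.

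A reader might also infer that the wrong assumption will be checked. That too goes beyond the text. The assumption is named correctly, the partial proportional odds model is the usual remedy for its failure, and no interaction test is planned as the check. Only the explanation is wrong.

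Finally, the level-by-level proportions and the dichotomised sensitivity analyses will give readers the full distribution and properly defined relative risks. That is right, and it limits the harm. The mRS range is a separate labelling slip that leaves the dichotomy unaffected.

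**Conclusion.** The point stands in a limited form. The reporting rule for ordinal outcomes is wrong as written, because the model provides a common odds ratio and no single relative risk for improving one level exists. This follows from the form of the model and needs no assumed figures. The size of any misstatement does need them. It arises only if the odds ratio is relabelled, and then it is about 1.4 to 1.5 times at a 20% control proportion, 2.5 to 3 times at 50% and 3.25 to 4 times at 60%, for odds ratios of 1.5 and 2.0. The incorrect explanation of proportional odds and the contradictory mRS range are confirmed as errors of wording.

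Severity is minor. mRS and GOSE are exploratory, General analysis principles treats all outcomes other than the primary as hypothesis generating, and neither the sample size nor the primary or secondary analyses are affected.

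**What to change.** - In Ordinal outcomes, replace the reporting sentence with: results are presented as a common odds ratio with 95% CI for being in a better category, across all cut-points.
- Give relative risks only for the dichotomised mRS (0–2 versus 3–6) and GOSE (above 5 versus 5 or below). These are already planned under Sensitivity analyses and can be estimated by the method under Dichotomous outcomes.
- In Assessments of underlying statistical assumptions, replace the bracketed explanation with: the same treatment odds ratio at every cut-point of the outcome. State that this will be judged from cut-point-specific odds ratios.
- Correct the mRS range to 0–6 in Table 1 and in the outcome list.

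The cost is SAP wording and results-table labels. No new data are needed and the main ordinal model stays the same; the cut-point-specific odds ratios are a short addition to the code. The change is best dated before the allocation code is broken.

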### Dichotomous outcomes

Dichotomous outcomes will be presented as proportions for each group with an annotation in the tables of the percentage of missing data per group. Dichotomous outcomes will be analysed using mixed-effects logistic regression with stratification variables as fixed effect and site as random effects. We will estimate the marginal effects to obtain RRs and confidence intervals of the RRs (based on ‘nlcom’ from Stata (StataCorp LLC, Texas, USA)) or G-computation in R. We have chosen to—as a primary analysis—investigate our count outcomes without dichotomisation. Inappropriate dichotomisation—even though widely used—results in lower power and possibly also faulty results [28, 30, 31].

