**Methods:**

DRAIN (*Danish RAndomised Trial of External Ventricular Drainage Cessation IN Aneurysmal Subarachnoid Haemorrhage*) is an international multicentre randomised clinical trial comparing prompt closure versus gradual weaning of the EVD after aSAH. The primary outcome is a composite of VP-shunt implantation, all-cause mortality, or EVD-related infection. Secondary outcomes are serious adverse events excluding mortality and health-related quality of life (EQ-5D-5L). Exploratory outcomes are modified Rankin Scale, Fatigue Severity Scale, Glasgow Outcome Scale Extended, and length of stay in the neurointensive care unit and hospital. Outcome assessment will be performed 6 months after ictus. Based on the sample size calculation (event proportion 80% in the gradual weaning group, relative risk reduction 20%, alpha 5%, power 80%), 122 participants are required in each intervention group. Outcome assessment for the primary outcome, statistical analyses, and conclusion drawing will be blinded. Two independent statistical analyses and reports will be tracked using a version control system, and both will be published. Based on the final statistical report, the blinded steering group will formulate two abstracts.

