## Methods

The DRAIN trial is an international multi-centre, 1:1 randomised, parallel-group, superiority clinical trial investigating gradual weaning versus prompt closure of EVD in patients with hydrocephalus following aSAH. The trial was registered at ClinicalTrials.gov with identifier no. NCT03948256 before inclusion of the first patient. The detailed trial protocol has been published elsewhere [9]. In short, all adult patients admitted to one of the participating neurosurgical departments with a diagnosis of aSAH and a need for EVD placement will be screened for enrolment. Each trial participant is allocated a unique patient trial number. Following successful treatment of the ruptured aneurysm, in eligible participants, the EVD resistance will be set to 10 cm H_2_O to ensure a uniform drainage production prior to intervention. An increase of drainage resistance to 15 cm H_2_O may be done if a high drainage volume is the only factor that keeps the patient from being randomised. When the participant fulfils all the inclusion criteria and none of the exclusion criteria, they will be randomised, and the allocated intervention (gradual weaning versus prompt closure) will be initiated immediately hereafter. Participants must fulfil the inclusion criteria within 18 days after ictus in order to be included in the trial. This statistical analysis plan follows the guidelines for statistical analysis plans [10].

Inclusion criteria:

> 18 years of ageDiagnosis of aneurysmal subarachnoid haemorrhage (aSAH)External ventricular drain (EVD) for > 6 daysaDrain output of < 220 mL/day at a resistance of 10 or 15 cm H2OStable or improving Glasgow Coma Scale (GCS) > 9 during the last 24 hSigned informed consent (from patient or next-of-kin)

Exclusion criteria:

Severe pre-existing (physical or mental) disability or severe co-morbidity that would lead to poor outcome even if the patient made a full recovery from the aSAHLife expectancy shorter than 48 hours after admission

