### Sample size and power justification

#### Sample size estimation

Data from the only previous randomised clinical trial suggest a VP-shunt implantation proportion of 63% in patients with acute need of CSF diversion following aSAH [5]. The mortality following aSAH is commonly quoted to be 27% to 50%, while 5.8% of patients develop an EVD-related infection [2, 7]. Assuming an incidence of either of the three components of the composite primary outcome (VP-shunt implantation, all-cause mortality, or EVD-related infection) within 6 months of 80%, an *α* = 0.05 (two-sided), and a *β* = 0.20, 2 × 122 participants are required to detect a 20% relative risk reduction or increase calculated using R (R Core Team, Vienna, Austria)*.* For composite outcomes, one missing component will result in missingness in the composite outcome. Number and percent missing due to a missing component will be stated in the report or in a diagram to avoid biased result, e.g. from death alone.

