### General analysis principles

Statistical analyses will be handled using the latest stable version of R (R Core Team, Vienna, Austria) and/or Stata (StataCop LLC, Texas, USA). The analyses will be carried out using the intention-to-treat principle where all randomised participants will be included in all analyses. The baseline characteristics will be presented for each group (Tables 2 and 3). The threshold for significance for all outcomes will be below 0.05, as the primary conclusions will be drawn based on the primary outcome [22]. All the remaining secondary and exploratory outcomes will be interpreted as hypothesis generating outcomes.

**Table 2 Tab2:** Baseline characteristics based on simulated data

	A	B
*n*	122	122
Age (mean (SD))	57.8 (0.90)	59.1 (0.50)
Gender, female (*n*, %)	85 (70.9)	90 (73.8)
Hypertension (*n*, %)	46 (37.2)	51 (41.3)
Aneurysm location (*n*, %)		
ICA	19 (15.6)	14 (11.5)
ACA/ACOM	50 (41)	56 (45.9)
MCA	16 (13.2)	11 (9.1)
Basilar artery	25 (20.5)	23 (18.9)
Vertebral artery/PICA	8 (6.3)	10 (8.2)
Pericallosa	4 (3.2)	2 (1.6)
Treatment modality		
Endovascular	50 (41)	56 (45.9)
Surgical	72 (59)	66 (54.1)
WFNS grade		
I	60 (49,2)	55 (45,1)
II	11 (9,0)	12 (9,8)
III	7 (5,7)	12 (9,8)
IV	29 (23,8)	24 (19,7)
V	15 (12,3)	19 (15,6)
Hunt Hess		
1–3	70 (57.4)	74 (60.6)
4–5	52 (42.6)	48 (39.4)
Glasgow Coma Score on admission		
15–14	42 (34.2)	46 (37.7)
13–9	21 (17.1)	17 (14.1)
8–3	58 (47.7)	55 (45.1)
Modified Fisher		
0–3	52 (42.8)	56 (45.9)
4	70 (57.2)	66 (54.1)
Modified LeRoux		
0–5	50 (41)	56 (45.9)
6–16	72 (59)	66 (54.1)
Nicotine use		
Current	21 (17.1)	18 (14.6)
Former	13 (10.4)	10 (8.2)
Never	88 (72.1)	94 (77.1)
Intubated at admission (*n*, %)	45 (36.9)	41 (33.6)
Acute hydrocephalus (*n*, %)	78 (63.9)	71 (59.1)

**Table 3 Tab3:** Summarised results of outcomes based on simulated data

	A	B	Estimate	*p*-value
*n*	122	122		
Primary outcome				
Composite outcome—*n* (%)	43 (35)	36 (30)	*RR (95%CI)* 1.01 (0.99 to 1.03)	0.05
Secondary outcomes				
SAE excl. mortality—median (IQR)	340	320	*median diff (95%CI)* 330 (329 to 349)	0.45
EQ-5D-5L -	60	56	*mean diff (95%CI)* 58 (55.1 to 59.2)	0.69
Fatigue Severity Scale	4.3	4.8	*mean diff (95%CI)* 4.5 (3.9 to 5.3)	0.05
Mean FSS (SD)	5.21 (1.8)	4.1 (1,4)	*mean diff (95%CI)* 4.6 (-4 to 14)	0.69
Clinical fatigue (FSS ≥ 4)	88 (72.3)	82 (67.2)	*mean diff (95%CI)* 3.4 (3.29 to 4.21)	0.34
Components of the primary outcome				

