#### Studies within the trial

A study within a trial (SWAT) is a study embedded in a host trial and should, similarly to randomised clinical trials, be predefined [34]. SWATs can among other things be used to investigate pathophysiological processes and inform possible future trials on design and conduct [35]. Multiple SWATs are embedded in the DRAIN trial (Table 4).

**Table 4 Tab4:** Studies within the DRAIN randomised clinical trial

	Study	Research question(s)	Methodology
1	Output as an independent predictor for closure/weaning success of external ventricular drainage in aSAH	Is the drain output an independent predictor of successful intervention? Is there an interaction between intervention and output?	Analysing the success rate of the first intervention attempt in a mixed effect logistic regression with drain output as a fixed effect and site as random effects
2	Time between EVD placement and closure/weaning as a predictor for success	Is timing an independent predictor for closure/weaning success?	Analyse the relationship between timing (days after EVD placement) and the first and/or the successful weaning attempt to assess whether time plays a role for weaning success with correction for the criteria for initiation of weaning
3	Profiling of drainage production over days with cumulated and daily volumes as a predictor for weaning success	Do different profiles of drainage production as a function over time exist—and is it possible to predict closure/weaning success based on the tendency of each profile?	Analyse volume of drainage production per day and assess whether morphology of different profiles has impact on closure/weaning success
4	Predictive risk factors for development of delayed hydrocephalus	Are there predictors in the initial clinical course of each patient with aSAH which would allow prediction of patients in risk of developing delayed hydrocephalus after initial discharge	Analyse associations between clinical parameters such as age, haemorrhage pattern, initial GCS, WFNS, ICP levels, drainage production, etc. and later development of delayed shunt-dependent hydrocephalus
5	Mortality after aSAH as a result of pre-disease comorbidities	Is long-term mortality affected for patients with aSAH, and affected by which comorbidities?	Analyse the mortality at 2 and/or 5 years after aSAH and the cause of death

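### Table 2 and the model omit drain output, GCS and timing at randomisation: a descriptive gap and a possible, probably modest, loss of precision

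*SAP article*

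**What the plan says.** **When participants are randomised.** Under Methods, eligibility requires an EVD for more than 6 days, drain output below 220 mL/day at a resistance of 10 or 15 cm H2O, and a GCS above 9 that has been stable or improving over 24 h. There is also an outer limit: "Participants must fulfil the inclusion criteria within 18 days after ictus". Allocation and the start of the intervention follow at once.

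**What the baseline table shows.** Table 2 (General analysis principles) has a row for "Glasgow Coma Score on admission" and one for intubation at admission. WFNS, Hunt Hess and modified Fisher appear without a time stamp. No row gives drain output, resistance, GCS or elapsed days at randomisation. The Results section says that Tables 2 and 3 show how data will be reported in the final manuscript.

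**What the model contains.** Dichotomous outcomes are to be analysed by "mixed-effects logistic regression with stratification variables as fixed effect and site as random effects", with a marginal RR by nlcom or G-computation. The stratification variables are modified Fisher grade, age and site.

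**How the plan regards the omitted values.** In Table 4, study 1 asks "Is the drain output an independent predictor of successful intervention" and whether output interacts with the intervention. Study 2 asks the predictor question about timing.

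**The concern.** In a trial that randomises a week or more after the haemorrhage, baseline is the moment of allocation. What matters then is how ready each participant is for the drain to be closed, and the eligibility criteria describe exactly that. A table built on admission status shows the original injury. It does not show whether the arms were alike when closure or weaning began. Output below 220 mL/day at 15 cm H2O is also not the same starting point as the same output at 10, and Table 2 cannot show how the two kinds of participant fell between the arms.

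The second stake is precision. The Outcomes section describes VP-shunt implantation as the consequence of failed EVD discontinuation, so a predictor of failed discontinuation could also predict the composite. Adjusting for such a predictor would narrow the confidence interval of the RR in a trial with little power to spare.

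**Working it through.** **1. Inputs.** From the SAP: 80% in the gradual weaning group, 20% relative reduction, two-sided alpha 0.05, power 80%, and "122 participants are required in each intervention group". The alternative is 0.80 × (1 − 0.20) = 0.64. Not in the SAP, hence assumed: the prognostic strength of the randomisation-time values for the composite.

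**2. The plan's own figure.**
- Pooled formula, mean proportion 0.72: n = [1.96·√(2·0.72·0.28) + 0.8416·√(0.80·0.20 + 0.64·0.36)]² / 0.16² = 122.4, rounded up to 123 per arm.
- Arcsine formula: n = 2·(1.96 + 0.8416)² / h², with h = 2·asin√0.80 − 2·asin√0.64, gives 121.3, rounded up to 122.
- Power with 122 per arm (pooled): 79.9%.

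The stated 122 reproduces.

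**3. Analytic range.** If the added covariates explain a further share R² of the outcome variance, the SE is multiplied by √(1 − R²) and the effective n is 122/(1 − R²).

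| Assumed R² | Effective n per arm | SE factor | Power |
|---|---|---|---|
| 0 | 122.0 | 1.000 | 79.9% |
| 0.02 | 124.5 | 0.990 | 80.7% |
| 0.05 | 128.4 | 0.975 | 81.9% |
| 0.10 | 135.6 | 0.949 | 83.9% |
| 0.20 | 152.5 | 0.894 | 87.9% |

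**4. Simulation of the change itself.** The fair comparison is the planned strata-adjusted model against the same model with covariates added, both giving a G-computation log RR, with 122 per arm and 80% vs 64%. Entries are the empirical SE with the covariates divided by the SE without them.

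| Assumed combined OR per SD | Two added covariates | Four added covariates | Power gain, two covariates |
|---|---|---|---|
| 1.0 | 1.00 | 1.01 | about 0 points |
| 1.25 | 1.00 | 1.01 | about 0 |
| 1.5 | 0.98 | 1.00 | about 1 |
| 2.0 | 0.95 | 0.97 | about 3 |
| 2.7 | 0.92 | 0.93 | about 6 |

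The two approaches agree. In a one-covariate simulation an OR of 2.0 per SD corresponded to R² of about 0.07 to 0.09 and an SE ratio of 0.960; √(1 − 0.08) = 0.959.

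**5. Room in the model.** Expected participants without an event: 122 × 0.20 + 122 × 0.36 = 24.4 + 43.9 = 68.3. Treatment, two strata and two covariates make five fixed coefficients, or 68.3/5 = 13.7 non-events each. Four covariates make seven, or 68.3/7 = 9.8 each, besides the site effect.

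**The case against.** The strongest reply is that nothing here is wrong. Adjusting for the stratification variables and reporting a marginal RR is a valid, pre-specified analysis, and further covariates are a matter of choice. That stands: the model part of this point concerns efficiency only.

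Several stronger readings are tempting, and the SAP does not support them.

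- *That precision is lost.* A reader might infer this from studies 1 and 2, but both pose prediction as an open question, and for success of closure or weaning. The six-month composite also counts death and infection. The eligibility limits on output and GCS narrow their range and may weaken any association.
- *That the primary RR is biased.* Allocation is concealed and stratified. Leaving out a prognostic covariate does not bias the marginal RR.
- *That the admission values are up to 18 days old.* The 18 days are an upper limit counted from ictus to meeting the criteria, not from admission. The EVD requirement implies only that the admission values will normally be about a week or more old.
- *That the mock GCS rows contradict eligibility.* The 47.7% and 45.1% shown at GCS 3–8 are simulated. Low GCS on admission followed by recovery above 9 is in any case consistent.

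It is also fair to object that four extra terms without a stated functional form would be more than about 68 non-events warrant. Two linear terms meet that. Finally, the SAP does not say that the exact GCS and resistance are recorded, only that eligibility requires them to be assessed. Studies 1 and 2 do imply that output and timing are held.

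**Conclusion.** The point holds in two parts of unequal weight.

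The descriptive gap needs no prognostic assumption. As planned, Table 2 cannot describe the arms at the moment of randomisation on the values that decided eligibility.

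The modelling part is conditional. The planned analysis is sound but may forgo precision. Two covariates gain from 0 to about 6 power points over an assumed combined OR of 1.0 to 2.7 per SD, and a gain of 3 points or more needs an OR of about 2 or above. These figures rest on 80% vs 64%, on assumed prognostic strength, and on the dichotomous model being the primary one. That last point is an inference: Table 3 reports an RR for the composite, while Table 1 types it as a count.

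**What to change.** Before unblinding:

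1. Add to Table 2, by arm and at randomisation: drain output with the resistance at which it was measured, GCS, days from ictus and days from EVD placement.
2. Pre-specify last 24-h drain output and days from ictus to randomisation as linear fixed effects in the primary logistic model, keeping the planned marginal RR.
3. Name the same two variables in the imputation model, where the SAP refers only to the most important baseline characteristics.
4. Keep the strata-only model as a sensitivity analysis.

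The cost is SAP wording and two coefficients, with under 1% added to the SE if neither variable is prognostic. No new data collection should be needed, provided the values assessed for eligibility were recorded; confirm this for GCS and resistance. With 243 participants already randomised, the choice is credible only if it is fixed while the analysis is still blinded.
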